### Ethical issues and informed consent

According to ethical guidelines, the researchers will abide by the Helsinki declaration. The participants' participation will be entirely voluntary, and they will have the right to withdraw from the trial at any time during the trial. The participants will be assured that participation in or withdrawal from the study will not cause any change to their regular treatment program. Participants will sign the informed consent (Extended data 3
^
37
^). The Institute of Physiotherapy Rehabilitation and Research of the Bangladesh Physiotherapy Association (BPA) has provided ethical permission (BPA-IPRR/IRB/06/16/2060) on 16
^th^ June 2022 to proceed with the study (Extended data 4
^
37
^). The trial has been registered with Clinical Trials Registry India (
CTRI/2022/11/047074) (Extended data 5
^
37
^). In case of any changes to the protocol, research team will notify to Institutional review board, the trial registry platform and in the later publications. The personal information of the participants will be confidential and stored unanimously in a dataset at the Department of nutrition and food technology at Jashore university of Science & Technology.

### Study status

This study has concluded the assignment of health clinics, training of intervention provider, ethical approval and applied for trial registration. We anticipate beginning this trial on 1
^st^ December 2022.

## Discussion

There is an increasing concern of LBP and vitamin D deficiency for chronic pain suffers that is leading the working people towards disability and inefficiency to work.
^
5
^
^,^
^
9
^ A non-randomized quasi experimental study
^
10
^ found therapeutic exercise and vitamin D oral supplementation is effective to reduce pain, replenish vitamin D3 level with short term results. Our study will meet the necessity of randomized systematic evaluation of therapeutic exercises and vitamin D supplement compensation in two different approaches, either by sun exposure, nutrition and healthy lifestyle or by taking oral supplements. We will evaluate outcome in both short term (2 months) and long-term effect after 6 months of stopping the intervention. The experimental group is the therapeutic exercise and booklet group because we assume a positive lifestyle and exercise can replace the role of oral medication supplement, as these were derived as a predictor in observational studies.
^
9
^

The methodological standard of the proposed trial adheres to the Enhancing the QUAlity and Transparency Of health Research (EQUATOR) guidelines to ensure the rigor of the study. As this is a two tailed hypothesis, we assume any treatment can be superior or both may have similar effect. The similar effect is also a positive finding, because oral vitamin D supplement have some adverse effects if taken for longer durations.
^
12
^ Moreover, if the study would have four arms including two interventions, a group with only vitamin D supplement and another with therapeutic exercise and a placebo vitamin D supplement, that could ensure true effects. However, researchers had to limit the study considering funding, scope of practice and complicated management issues. As outcome indicators pain and vitamin D3 levels will be used as primary outcomes and disability as secondary outcome, because previous research suggests disability as a consequence.
^
36
^ BPI measures not only pain severity, but also pain affective interference and pain physical interference,
^
10
^
^,^
^
30
^ that is consistent to the effect of intervention.

The findings of this study may provide important insights into the rehabilitative role of therapeutic exercise in chronic low back pain (CLBP). Beyond its established benefits for musculoskeletal function, exercise may influence the production, absorption, deposition, and overall metabolic function of serum vitamin D, thereby enhancing pain modulation and functional recovery. Evidence suggests that exercise improves vitamin D metabolism and reduces musculoskeletal pain through mechanisms such as modifying sensory neuron excitability and regulating both anti-inflammatory and pro-inflammatory cytokines, ultimately contributing to remission of disability.
^
7
^ If lifestyle education delivered through the booklet demonstrates positive behavioral changes, this could open new avenues for rehabilitation by promoting self-regulation of vitamin D3 levels and supporting natural remission of CLBP. Moreover, the combined approach of therapeutic exercise and supplementation may offer strategies to reduce recurrence or delay the episodic pattern of pain, adding to the repertoire of non-pharmacological options for CLBP therapy. Overall, these findings highlight the potential to broaden rehabilitative strategies by combining exercise-mediated regulation of vitamin D metabolism with conventional physiotherapy, thereby introducing innovative, evidence-based approaches for the management of chronic low back pain.

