Chronic low back pain (CLBP) has been associated with vitamin D deficiency, which affects calcium metabolism, bone health, and muscle function. Deficiency may lead to osteomalacia, muscle weakness, and impaired neuromuscular control, increasing spinal instability and pain. Additionally, low vitamin D levels can elevate pro-inflammatory cytokines, intensifying pain sensitivity and contributing to chronic musculoskeletal disorders.
^
8
^ Clinical studies have reported a higher prevalence of vitamin D deficiency among patients with CLBP compared to healthy controls, suggesting a potential association between deficiency and pain severity.
^
17,
18
^ Vitamin D supplementation has been explored as a supportive measure in CLBP due to its role in bone health, muscle strength, and inflammation regulation.
^
19
^ Correcting deficiency may improve musculoskeletal function and reduce pain sensitivity, with clinical trials reporting symptomatic improvement in deficient patients.
^
20,
21
^ However, meta-analyses indicate limited overall efficacy, suggesting benefits may be restricted to those with confirmed deficiency, while excessive intake carries risks such as hypercalcemia and kidney stones.
^
22
^

This study hypothesizes that multidimensional comprehensive management through therapeutic exercise combined with an education booklet on sun exposure, nutrition, and lifestyle (TEB) will be superior to therapeutic exercise with oral vitamin D supplementation (TED) in patients with chronic low back pain and vitamin D deficiency. Specifically, it is expected that participants in the TEB group will demonstrate greater improvements in pain symptoms, serum vitamin D levels, and disability status compared to those in the TED group, with these effects observed at both 2 and 6 months following baseline recruitment. Following the study hypothesis, this trial holds clear clinical significance: for clinicians, it offers evidence to guide treatment choices between exercise combined with education or vitamin D3; for patients, it evaluates accessible, low-cost strategies that may improve pain and function; and for researchers, it provides rigorous comparative data to inform future studies on scalable interventions for CLBP.

The specific objectives are:

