## Participant timeline

### Sample size

The sample size for this trial was determined based on methodological standards used in low back pain research. Previous studies have indicated that randomized controlled trials in chronic low back pain require a minimum of 152 participants to detect clinically meaningful superiority differences, with a significance level (α) of 0.05, statistical power of 80%, and a 95% confidence interval. Considering potential attrition, we plan to recruit additional participants to ensure adequate statistical power and robustness of findings.
^
34,
35
^

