### Data analysis

Data will be analyzed based on its nature. Calculation and data auditing will be done using Microsoft Excel 2016. Data will be analyzed by SPSS version 23, and R-4.2.1 for Windows. Eligibility for parametric analysis will be checked using bell’s curve, skewness, kurtosis, Kolmogorov–Smirnov test and Shapiro–Wilk test. Continuous variables will be represented by using an arithmetic mean and standard deviation. Categorical data will be represented by percentage (%) and frequency. Baseline characteristics between groups will be compared using chi-square tests for categorical variables and independent t-tests or Mann–Whitney U tests for continuous variables, depending on data distribution. Normality will be assessed using the Shapiro–Wilk test. For within-group comparisons across time points (baseline, 2 months, and 6 months), repeated measures ANOVA will be applied for parametric data, with Greenhouse–Geisser correction if sphericity is violated; the Friedman test will be used for non-parametric data. Between-group differences over time will be analyzed using mixed-model repeated measures ANOVA, which accounts for group × time interactions, or generalized estimating equations (GEE) if assumptions are not met. Post-hoc pairwise comparisons will be adjusted using Bonferroni correction. Effect sizes (Cohen’s d or partial eta squared) will be reported to indicate the magnitude of differences. All analyses will be conducted at a two-tailed alpha level of 0.05, and intention-to-treat principles will be applied to handle missing data.

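### The Discussion counts a similar effect as a positive finding, but hypothesis, sample size and analysis address superiority only and set no margin, which invites reading a non-significant result as similarity

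*Protocol article*

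**What the plan says.** Three parts of the protocol article describe a superiority trial.

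- **Introduction.** The hypothesis is that exercise plus the education booklet (TEB) does better than exercise plus oral vitamin D (TED) on pain, serum vitamin D and disability, at 2 and 6 months.
- **Sample size.** Earlier low back pain trials are said to "require a minimum of 152 participants to detect clinically meaningful superiority differences". Power is put at 80% and alpha at 0.05.
- **Data analysis.** Between-group differences are tested by mixed-model repeated measures ANOVA, or GEE if assumptions fail. "All analyses will be conducted at a two-tailed alpha level of 0.05". Cohen's d or partial eta squared will be reported, with no threshold attached.

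The Discussion then adds a third possible outcome: "As this is a two tailed hypothesis, we assume any treatment can be superior or both may have similar effect". It goes on: "The similar effect is also a positive finding, because oral vitamin D supplement have some adverse effects if taken for longer durations".

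The article gives no equivalence or non-inferiority margin, no definition of similar, and no rule that sets a confidence interval against a limit.

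**The concern.** A two-sided test of a difference either rejects the null hypothesis or does not. It has no outcome that means the arms are alike. The Discussion nevertheless derives similarity from the two-tailed hypothesis, as what is left when neither arm is superior. Under the planned analysis that remainder is non-significance.

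Non-significance can come from a truly small difference, but also from noise, dropout or too few patients. If it is taken as a positive finding, a trial that merely failed to settle the question could be cited for using a booklet in place of supplements. The stakes are real, because the Abstract expects the findings to inform clinical guidelines. Both arms also receive the same exercise programme, so a null result on pain would be equally compatible with neither adjunct adding anything.

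**Working it through.** **Inputs from the article.** Two-sided alpha 0.05 (Data analysis); power 80% and a minimum of 152 participants, for superiority (Sample size).

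**Assumptions, because the article does not state them.** 152 is the evaluable total; allocation is 1:1, so 76 per arm; there is one unadjusted post-baseline comparison; differences are in SD units; the normal approximation applies.

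**The plan's own figure.** No effect size or SD is given, so 152 cannot be derived forward. It can only be solved backwards:

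- SE = √(2/76) = 0.162 SD
- Detectable difference = (1.960 + 0.842) × 0.162 = 0.4545 SD

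If 152 were the number per arm, the same formula gives 2.802 × √(2/152) = 0.321 SD.

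**Precision.** The 95% CI half-width is 1.960 × 0.162 = 0.318 SD. Even an observed difference of exactly zero would leave true differences of about 0.32 SD in either direction unexcluded.

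**Chance of a non-significant result** when TEB is truly worse by d: 1 − Φ(d/SE − 1.960).

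| True disadvantage (SD) | Non-significant, 76 per arm |
|---|---|
| 0.2 | 77% |
| 0.3 | 54% |
| 0.4 | 31% |
| 0.4545 | 20% |

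**Range over the assumed sample.** With 65 evaluable per arm, the chances at 0.3 and 0.4545 SD rise to 60% and 26%. With 152 per arm, SE = 0.115, the half-width is 0.22 SD, and the chance at 0.3 SD is 1 − Φ(2.615 − 1.960) = 26%. Adjustment for baseline would also narrow the interval. None of these changes supplies a margin.

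**What a formal claim would need.** The article gives no margin, so those below are illustrative only. All figures are for one outcome with a true difference of zero.

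- Non-inferiority (one-sided 0.025): n per arm = 2 × [(1.960 + 0.842)/margin]²; power with 76 per arm = Φ(margin/SE − 1.960).
- Equivalence by 95% CI: n per arm = 2 × [(1.960 + 1.282)/margin]²; power = 2Φ(margin/SE − 1.960) − 1, or zero where this is negative.

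| Margin (SD) | Non-inferiority: total for 80% power | Power with 152 | Equivalence: total for 80% power | Power with 152 |
|---|---|---|---|---|
| 0.3 | 350 | 46% | 468 | 0% |
| 0.4 | 198 | 69% | 264 | 39% |
| 0.4545 | 152 | 80% | 204 | 60% |
| 0.5 | 126 | 87% | 170 | 74% |

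With a 90% CI, equivalence power with 152 is 16%, 59%, 75% and 85% at these margins.

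If the claim must hold for both pain and 25(OH)D, power falls further. At 0.4545 SD, and if the two outcomes were independent, it would be 0.80² = 64% for non-inferiority and 0.60² = 36% for equivalence by 95% CI.

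**The case against.** The strongest reply is that the article nowhere says a p-value above 0.05 will be called similar. The wording "we assume any treatment can be superior or both may have similar effect" can be taken as a remark about what may be true, followed by a reason why that would be welcome. The analysis section contains no similarity claim and promises effect sizes. The sentence stands in a Discussion, and the hypothesis, the sample-size aim and the tests agree with one another. A separate analysis plan may exist.

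Much of this stands. That a null result would be reported as similarity is an inference, and the defensible statement is that the text invites it. The reply does not remove the point, because the Discussion ties similarity to the two-tailed hypothesis and calls it a finding, and no planned result other than non-significance could produce that finding. This is a statement about what the test can show, not a detail left for an analysis plan.

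A reader might also infer that the trial cannot fail. The article does not support that: it allows either arm to be superior, and significant superiority of TED would contradict the hypothesis. At a true disadvantage of 0.4545 SD, that would be detected about 80% of the time under the assumptions above.

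**Conclusion.** The point holds as an inconsistency. The Discussion promises a conclusion that the superiority hypothesis, sizing and tests cannot deliver. Only significant superiority of TED would count against the booklet; every other result has a favourable reading available.

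The logical defect does not depend on any number. Its size does. Under the stated assumptions the 95% CI half-width is about 0.32 SD, and a true 0.3 SD disadvantage goes undetected about 54% of the time (26% to 60% over the sample sizes tried).

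A reader might take 0.45 SD as the difference the trial was designed to detect. The article states none; the figure is solved backwards from 152 and serves only as an illustration.

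This should be fixed. It concerns how a result is interpreted and changes no endpoint, test or estimate.

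**What to change.** Delete or reword the two Discussion sentences. A non-significant result should be described as inconclusive and reported with the between-group difference and its 95% CI for BPI pain and for serum 25(OH)D. This costs a few words and no patients. The sponsor loses the positive reading of a null result.

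If the sponsor does want to claim that the booklet is similar or not worse, the protocol should, before any results are seen:

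- set a justified margin for each primary outcome, in BPI points and in ng/mL;
- state the confidence-interval rule, its level, and whether both outcomes must pass;
- choose the matching objective: non-inferiority fits the stated reason (avoiding adverse effects of supplements), equivalence only if two-sided similarity is meant;
- state the power that the planned sample gives for that claim.

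This option is not free. At narrow margins, or when both outcomes must pass, 152 patients may give low power and more may be needed. Timing matters too: the Monitoring section gives the research team access to interim results, and a margin chosen after such access would carry little weight.
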